## Abstract

Research has indicated strong associations between posttraumatic stress and cardiovascular disease (CVD) risk. Individuals with posttraumatic stress disorder (PTSD) tend to show patterns of elevated CVD risk earlier in life than the general population. The need for developing effective interventions for CVD risk-reduction in PTSD is increasingly evident. The present paper outlines the theoretical background and methodological details for the protocol of an ongoing NHLBI-funded longitudinal study (entitled *Investigating Cardiac Health of Adults with Trauma*) to test the effects of a health behavior intervention as an adjunct to standard trauma therapy in PTSD. The health behavior intervention addresses CVD-related health behaviors (physical activity, nutrition, sleep, and stress). Participants are randomized to the health behavior intervention plus standard trauma therapy condition or a standard trauma therapy control group. Outcome assessments are conducted before and after the 12-week intervention program in the experimental group, and 12 weeks apart for the control group, as well as at 6-month and 12-month follow-up time points. The outcomes include laboratory measures of CVD risks/markers (e.g., endothelial function, arterial stiffness, lipids, blood pressure), actigraphy-based measures of physical activity and sleep, and standardized self-report measures of sleep, physical activity, nutrition, stress, and psychological functioning (e.g., PTSD symptoms, depressive symptoms). The study findings will provide valuable data on the effectiveness of the health behavior intervention in producing predicted changes in the target CVD-related behaviors/markers.

## Introduction

Strong relationships between PTSD and cardiovascular disease (CVD) risk have been identified, with numerous studies indicating those with posttraumatic stress disorder (PTSD) are at greater CVD risk, earlier in life (Browne et al., 2021; Kibler et al., 2018; Reis et al., 2023; Seligowski et al., 2024; Smith et al., 2020a; Sumner et al., 2020). The need for developing effective interventions for CVD risk-reduction in PTSD is increasingly evident. Compared to the cumulative evidence concerning elevated CVD risk in PTSD, relatively little research has addressed CVD risk-reduction in this population (Bourassa et al., 2021; Farr et al., 2014; Krantz et al., 2022; Li et al., 2024; National Heart Lung and Blood Institute, 2018; Scherrer et al., 2020). One study revealed that Veterans whose PTSD symptoms improved while treated in Veterans Affairs (VA) PTSD specialty clinics did not show significant improvement in CVD risks (Scherrer et al., 2020). Thus, adjunctive treatments, such as health behavior interventions, may be necessary as supplements to traditional psychotherapy for PTSD to reduce CVD risks. Health behavior interventions are needed that specifically address unique aspects of PTSD symptom presentation, which serve as barriers to healthy behaviors (e.g., avoidance of physiological arousal/activation, nightmares/sleep disruption, and cognitive responses to stress) and may not be adequately targeted with standard mental health treatments (Farr et al., 2014; Li et al., 2024; National Heart Lung and Blood Institute, 2018; Scherrer et al., 2020).

Heightened awareness or fear of bodily arousal symptoms, such as increased heart rate or shortness of breath, have been associated with less physical activity and lower ratings of exercise motivation in PTSD (Crombie et al., 2023; Hall et al., 2015; Harte et al., 2015). In conjunction with anxiety reactions, the fear of bodily arousal can be conceptualized as anxiety sensitivity, which is commonly reported among those with PTSD (Asmundson and Stapleton, 2008; Crombie et al., 2023; Stanley et al., 2017). Anxiety sensitivity may lead to avoidance of exercise (Olthuis et al., 2023). Conversely, there is experimental evidence that engaging in physical activity can decrease anxiety sensitivity (Broman-Fulks et al., 2004; Crombie et al., 2023; Hall et al., 2015), thereby reversing the negative cycle of avoidance at least temporarily. These effects are theorized to occur through exposure and desensitization to internal arousal cues (Broman-Fulks et al., 2004). Potential fear of arousal symptoms may underscore the need to begin slowly when implementing physical activity for individuals with PTSD who have been sedentary. Research and health behavior theories support the notion that abrupt increases in activity are not as likely to be maintained (Sabourin et al., 2011). Such abrupt changes may be more difficult when one has hypersensitivity to arousal (Sabourin et al., 2011). Therefore, our experimental intervention was designed to be sensitive to the specific needs of participants with PTSD. Participants report positive responses to being able to work at their own pace and feel supported by interventionists who “met them where they are” regarding physical activity. In addition, our strategy of having interventionists walk with participants during designated sessions allows the interventionist to address perceptions of arousal in the moment, and to encourage continued exposure and desensitization while providing support. Hall et al. (2020) indicated that increasing physical activity is feasible and can enhance aerobic performance and metabolic measures among older military Veterans with PTSD.

There is evidence that unhealthy lipid levels and higher weight are more prevalent among individuals with PTSD (Bharti et al., 2022; Kibler et al., 2018; Rossi and Isnard, 2023); 75–85% of adults with PTSD meeting criteria for overweight and 45–50% for obesity. These findings are consistent with the hypothesis that over-eating and consumption of high-fat foods may contribute to CVD in PTSD (Hirth et al., 2011). Although lipid levels are determined by additional physiological factors beyond eating, research of this issue generally indicates behavioral factors such as food choices and physical activity confer at least an interactive effect with genes and medical factors (Vinson et al., 2008). A recent study found that elevated triglycerides in PTSD were associated with greater blood pressure levels (Bhargava et al., 2024). One of the key theoretical concepts implicated in the eating behavior of those with PTSD is that eating is a mechanism for coping. Across trauma types, binge eating to cope with trauma-related stressors has been observed (Harrington et al., 2010; Tagay et al., 2014). Binging may represent a form of dissociation or a way of focusing attention away from distressing thoughts and negative emotion (Huston et al., 2019). Another phenomenon related to regulation of eating in PTSD is that abused individuals often have a disrupted sense of self-worth and attractiveness. This can, in turn, manifest in diminished self-care, such as overeating and physical inactivity (Gustafson and Sarwer, 2004; Wolf and Elklit, 2018).

Recurring trauma-related nightmares in PTSD and consequent behavioral conditioning of sleep avoidance are disruptive, prolonging sleep latency and contributing to irregular bedtimes (Lamarche and De Koninck, 2007; Schumm et al., 2023). Moreover, these types of disruptions in sleep have relevance for CVD risk/outcomes (Covassin and Singh, 2016; Huang et al., 2020; Makarem et al., 2019; Scherrer et al., 2020). The study by Scherrer et al. (2020) demonstrated that sleep disorders mediated PTSD/CVD associations. Thus, sleep interventions may enhance CVD risk-reduction efforts (Javaheri et al., 2020; Makarem et al., 2019). Psychotherapies for PTSD have not typically addressed sleep problems directly or systematically, and sleep outcomes following therapy have not generally been assessed (Galovski et al., 2009; Pruiksma et al., 2016). The limited number of CBT interventions that have focused specifically on sleep in PTSD have resulted in improved sleep (Krakow et al., 2001; Moore and Krakow, 2007). Therefore, additional research on this area of treatment may further inform the potential for health behavior intervention to impact health in PTSD. Relationships of sleep with physical activity and stress (Eid et al., 2021; Zhu et al., 2021) may help in explaining the potential role of sleep in associations between PTSD and CVD risk (Scherrer et al., 2020).

Stress-related and emotional factors have been identified as an early candidate mechanism for PTSD/CVD relationships, with various responses to acute and chronic stress being implicated in this relationship (Smith et al., 2020a,b). For example, PTSD severity was shown to be related to delayed cardiovascular recovery following a general (not trauma-related) laboratory oral speaking stressor (Kibler, 2018). Delayed cardiovascular recovery in the lab has been associated with greater carotid intima-media thickness, as well as elevated resting blood pressure measured 3 years after lab assessment of recovery (Steptoe et al., 2006; Steptoe and Marmot, 2005). Perceived threat (a pervasive maladaptive cognitive response in PTSD) mediated these physiological disruptions (Kibler, 2018). Research has identified cognitive appraisals, including perceived threat, as key factors to address in PTSD (Iverson et al., 2015). Although the implications of cognitive appraisals for health behaviors in PTSD have not been adequately researched, relationships of appraisals to stress are evident, and Lazarus and colleagues' Cognitive Appraisal Theory (Lazarus and Folkman, 1984) suggests that the types of disrupted cognitions evident in PTSD may interfere with the pursuit of healthy behaviors such as physical activity (Folkman et al., 1986). Interventions to address cognitive appraisals may reduce stress-related CVD risk in PTSD by enhancing the ability to cognitively cope with stressors and engage in healthy behaviors.

The purpose of the present paper is to detail our approach to the study protocol, focusing on the scientific rationale and methodological details. It is hypothesized that the healthy lifestyle intervention will result in greater improvement in vascular function (i.e., endothelial function, arterial stiffness), physical activity, nutrition, sleep, and stress, above and beyond the effects of standard trauma therapy.

## Methods

### Participants

We plan to randomize a total of 212 participants, ages 18 and over, to the two study conditions. Anticipated demographics of the overall sample, based on current data from proposed recruitment sites and prior studies recruiting from the PTSD population, are ages 37 ± 10 (mean ± SD), approximately 72% female, avg. of 12th grade education ± 3 years, and race/ethnicity composed of 64% Caucasian, 21% Hispanic-White, 10% African-American, 3% Caribbean Black, and 2% Hispanic-Non-White. Adults ages 18 and older are recruited from the community, local clinics, and via online advertisements. Criteria for inclusion are: PTSD or subthreshold PTSD [evidenced by ≥ 4 PTSD symptoms (including ≥ 1 re-experiencing symptom) endorsed as 2 or higher (moderately bothersome) on the Posttraumatic Stress Checklist (PCL-5)], the presence of at least one health risk (low physical activity, nutrition does not meet standard recommendations, overweight, sleep disruption), and ability to exercise at a moderate level. Concurrent trauma-focused psychotherapy is required through the 12-week intervention phase of the project and is provided by the project if the participant is not already receiving trauma-focused therapy in the community. On an ongoing basis, the project coordinator verifies the therapy and frequency. Although chronic illnesses are not exclusionary, medications for controlling lipids or blood pressure (e.g., beta blockers, diuretics, ACE inhibitors, statins, PCSK9 inhibitors) are exclusionary, as they would impact the lipid and blood pressure outcomes. Participants may be considered if they are able to consult with their medical provider about temporarily discontinuing these medications long enough for the medication to not be active in the system. Comorbid psychiatric conditions (e.g., depression, personality disorders, substance use disorders) are not exclusionary, as this would result in an unnaturally narrow selection of participants with PTSD. Consistent with standards for intervention studies in PTSD (Mulick and Naugle, 2010; Resick et al., 2002, 2015), those on psychopharmacological medications will be included if the regimen has been maintained as stable for ≥2 months prior to enrollment. This study is approved by the appropriate University Institutional Review Board (IRB). Written informed consent is obtained from all participants at the time of the first outcome assessment (baseline) by the laboratory research assistant(s). As with any human research, a participant may discontinue either intervention condition or any other aspect of the longitudinal study at any time, regardless of the reason.

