### Measures

#### Outcome assessment sessions

Four assessment sessions provide an indication of treatment-related outcomes. These sessions are conducted in person at a University-based laboratory at our study site in Ft. Lauderdale, FL (U.S). The first assessment (baseline) is conducted prior to the first week/study onset in each condition. The second assessment (post-treatment) is conducted at the 3-month time point (after the last healthy lifestyle session in the experimental condition). The third and fourth assessments (follow-up) are conducted at the 6-month and 12-month time points. Each assessment session consists of the same outcome measures: blood pressure, lipids, body mass index (BMI), arterial stiffness, endothelial function, heart rate variability (HRV), physical activity, nutrition, perceived stress, sleep (quantity, efficiency, quality, and restfulness), and psychological measures (PTSD symptoms, depressive symptoms). Results of the lipid measures and blood pressure are reviewed with participants following each assessment, and it is recommended to those with clinically elevated levels that they consult with their primary care physician or other medical provider about such findings.

Due to potential confounding effects on lipids and/or blood pressure, participants are asked to refrain from caffeine and strenuous exercise for 3 h, and smoking for 30 min, prior to assessment sessions. These sessions are scheduled early in the morning (approx. 8:30 a.m.) due to the requirement of fasting for lipid assessment. Non-compliance with restrictions requires rescheduling. After the lipid assessment a standardized snack (granola bar, and water/juice) is provided. A doctoral research assistant (under the direction of the PI) leads each assessment session. The data collection for the assessment sessions lasts approximately 90 min. Assessment of the following variables involving physical measurement is conducted first:

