#### Medication use

Medication use is assessed by self-report during the screening period to determine participant eligibility, ensuring that current medications do not confound study outcomes. At each lab assessment time point, participants are asked to report any changes in medication use. An open-response option is provided to capture detailed information, allowing participants to type in the names and dosages of their specific medications. This approach enables comprehensive and precise documentation of medication use across all study phases.

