### Procedures

#### Recruitment and enrollment

Participants are recruited from university and community-based clinics, private practices, and from the community using written and online notices/flyers. Locations for recruitment within the community using written flyers include community college campuses, bus/train stops, parking garages, public bulletin boards, public libraries, public restrooms, convenience stores, shopping centers/grocery stores with community bulletin boards, laundromats, religious centers (churches), community centers, public parks, and recreation centers. Online notices for the study are posted on Craigslist, Facebook, and Instagram. Participants are also recruited by other participants within the study. Potential participants call a private central phone number or respond to the study email address to express interest in the study. Volunteers are then screened by phone to assess basic study inclusion and exclusion criteria and to provide additional details about the study. Randomization to study condition is performed by the project coordinator following the initial phone contact (using the flip of a coin). Neither the participants nor the investigators are blinded for this trial. At the baseline/pre-intervention assessment, informed consent and additional screening assessments are administered to further evaluate and verify eligibility based on PTSD symptoms and the presence of at least one risk factor targeted by the intervention (e.g., physical inactivity, overweight status, sleep difficulties). All records are kept confidential. A list of participant names linked to their code numbers is kept in a secured file and accessed by study coordinators for project-related communications. Only code numbers are used to organize participant study data. The coded project data are kept in a separate secured file. Participant compensation consists of a $50 gift card for each of the pre-, post-, and follow-up assessment sessions, and a $10 gift card for each intervention session completed by the participant.

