### Protection against risks

At the baseline assessment, written informed consent is sought by the advanced doctoral student assistant, who verbally evaluates the participant's understanding of the study and consent form. All participants are carefully monitored throughout all assessment procedures. The PI ensures proper clinical care to study candidates who appear to be experiencing strong emotional reactions during any part of the study, and works with the project staff to help participants who require additional assistance coordinating care. Because depressive symptoms commonly co-occur with PTSD symptoms, participants are monitored at each assessment session for depressive symptoms and suicidality via the BDI-II. Experimenters/interventionists are trained to assess suicide lethality and are provided with specific steps to follow in the event that a participant is actively suicidal. Clinic support staffs are available to assist with a crisis during the assessments. The experimenter will be instructed to contact the PI when a participant experiences active suicidal intent, and appropriate clinical coverage (licensed psychologist) is designated at any time that the PI is not available. Non-lethal suicidal ideation is handled in the manner described above, with the study staff and PI ensuring adequate clinical follow-up of such symptoms.

To minimize the risk of infection for the finger stick, universal precautions for sanitary collection and handling of human blood samples are followed. In addition, participants are free to decline any procedure that may be distressing for them, and/or withdraw from the study at any time. Therefore, participants may decline or terminate the finger stick procedure at any time. To minimize the risk associated with the exercise intervention, participants are advised to get physician clearance for participation in an exercise regimen.

All records are kept confidential. Only code numbers are used to organize participant data. The coded project data will be kept in separate secured file. No information about the participant will be released to outside parties without consent. Under certain circumstances, records may be reviewed for audit purposes by authorized University employees who will be bound by the above described provisions of confidentiality. No identifying information will be included in any project presentations or publications.

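### Volunteers may stop lipid or blood pressure drugs to qualify, but consent is placed at the baseline visit, so the stop comes before consent and before eligibility is verified

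*Protocol article*

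**What the plan says.** The Participants section says that drugs controlling lipids or blood pressure "are exclusionary, as they would impact the lipid and blood pressure outcomes". It then makes an exception: a volunteer may be considered if able to consult a medical provider about "temporarily discontinuing these medications long enough for the medication to not be active in the system".

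The Medication use section sets the time at which this criterion is judged: "Medication use is assessed by self-report during the screening period to determine participant eligibility". Under Recruitment and enrollment, screening starts with a phone call that covers basic inclusion and exclusion criteria and gives further details of the study.

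Consent is placed at baseline in three sections:

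- Participants: "Written informed consent is obtained from all participants at the time of the first outcome assessment (baseline").
- Recruitment and enrollment: at the baseline assessment, "informed consent and additional screening assessments are administered to further evaluate and verify eligibility based on PTSD symptoms" and on having at least one targeted risk factor.
- Protection against risks: "At the baseline assessment, written informed consent is sought by the advanced doctoral student assistant", who also checks the participant's understanding verbally.

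Outcome assessment sessions lists blood pressure and lipids among the measures taken at every session, baseline included. It adds: "Assessment of the following variables involving physical measurement is conducted first" and "The data collection for the assessment sessions lasts approximately 90 min".

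**The concern.** Stopping a prescribed statin or antihypertensive only to meet a study criterion is a change in care caused by the study. A volunteer would normally make such a change after giving consent and after the study had established that the person qualifies. Here both steps appear to come afterwards.

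Two groups are exposed. Those who go on to enrol have been through the washout without having consented to the research. Those who stop a drug and then decline consent, or fail the PTSD or health-risk check at baseline, have interrupted treatment and never enter the trial. The Introduction describes people with PTSD as being at greater cardiovascular risk, and earlier in life, so an interruption of these drugs is not trivial.

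This is a matter of protecting volunteers. It makes no claim about the effect estimates. Randomization after the phone contact, also before consent, is a separate point.

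**Working it through.** The plan gives no figure to reproduce. The check is one of sequence, made by setting the sections side by side.

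1. **Purpose of the exception.** The exclusion exists because the drugs would affect the lipid and blood pressure outcomes (Participants). The exception serves that purpose only if the drug is already inactive when the first lipid and blood pressure values are taken.
2. **When those values are taken.** At the baseline session, with the physical measures first (Outcome assessment sessions).
3. **When consent is given.** At that same baseline session, for all participants (Participants; Recruitment and enrollment; Protection against risks).
4. **Time available between steps 3 and 2.** Part of one morning visit with about 90 minutes of data collection. Whatever the drug, the period needed for it to become inactive cannot be placed there.
5. **When eligibility is verified.** PTSD symptoms and the presence of a risk factor are verified at baseline, together with consent (Recruitment and enrollment). Medication use is judged earlier, in the screening period (Medication use).

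The resulting order for a volunteer on one of these drugs is:

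phone screen with medication self-report → consultation with own provider → drug stopped and washed out → baseline visit with consent, verification, and lipid and blood pressure measurement.

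The drug stop therefore precedes both written consent and verification of eligibility.

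**Could consent be given at one visit and measurement follow at a later one?** No such split is described. The rescheduling rule under Outcome assessment sessions concerns the pre-visit restrictions (caffeine, strenuous exercise, smoking, fasting), not medication.

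**Size.** The article gives no count or share for this route. For illustration only, with assumed share p of the 212 planned participants, the number affected is 212 × p:

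| Assumed p | 212 × p | Rounded |
|---|---|---|
| 1% | 2.12 | 2 |
| 5% | 10.6 | 11 |
| 10% | 21.2 | 21 |

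Volunteers who stop a drug and then do not enter the trial would be additional to these, and the article gives no rate for them either.

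**The case against.** - **The order is inferred.** No single sentence says that the drug is stopped before consent, the exception is discretionary, and the sections do not contradict one another. That is correct. But the order follows from the stated purpose of the exclusion and the stated time of consent, and it needs no outside fact beyond a washout not fitting into a single visit.
- **The full protocol may hold an earlier consent step.** An article does leave procedural detail to the full document. This article, however, is not silent: it states the time of consent in three sections, once for all participants. If an earlier step exists for this group, that statement is wrong for them and needs correcting.
- **A first eligibility screen and study information come earlier.** The phone contact does cover basic criteria and study details, which lowers the chance that someone stops a drug and then proves ineligible. The health-risk criterion is also broad, and the subthreshold PTSD rule asks for only four symptoms. This limits how often the harm would occur. It does not supply written consent, and the article itself leaves verification to baseline.
- **The volunteer's own provider is involved.** This is a real safeguard for the clinical decision, but clinical advice is not consent to research.
- **Few may be affected.** With an expected age of 37 ± 10, use of these drugs may be uncommon. The number is unknown and could be zero, which bears on how serious the point is, not on whether the sequence is right.
- **Moving consent ahead of randomization would largely solve this too.** It would, provided the washout followed that consent. The point still needs stating, because the drug stop has to be tied to consent explicitly.

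**Conclusion.** The concern holds. As the article is written, a volunteer who qualifies by stopping a lipid or blood pressure drug does so before written consent and before the PTSD and health-risk criteria are verified. The conclusion rests on two readings: that the exception is meant to give drug-free baseline values, as the reason for the exclusion implies, and that consent and baseline measurement share one visit, as the article describes.

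The plan should be changed, although the point does not threaten the trial's results. The number of people involved is not given; the illustrative range is about 2 to 21 of 212, and the true number may be nil. The provider's role and the phone screen reduce the risk without removing it. Confidence is medium, because the order is deduced from several rules and the full protocol was not available.

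**What to change.** For volunteers entering by this route only:

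1. Obtain written or remote electronic consent, including a check of understanding, before they are invited to discuss stopping a drug for the study.
2. At that contact, confirm the self-report criteria (PCL-5 and health risk) remotely where feasible, so that nobody stops a drug and is then found ineligible on those grounds.
3. Record the dates of the washout and any events during it.
4. Leave with the treating provider the decision whether and how to stop.

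The cost is one amendment, one earlier remote contact per affected volunteer and some coordinator time. The PCL-5 is already a self-report measure completed by online computer assessment, so no new test is needed. Its current use is within in-person sessions, however, so remote completion and a remote version of the understanding check need a short written procedure. If the study already obtains consent before any such drug stop, a sentence saying so in the Participants section would be enough. The abstract describes the study as ongoing, so the change can still protect volunteers yet to be screened.
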